#### Recording of AEs

The operational definitions of the AEs collected from randomization to hospital discharge are given in Textbox 10 and include two types of events:

Air leaks: ASA is a well-recognized risk factor for air leak. Higher HiFlo rates (>2 L/kg) can mimic the effects of CPAP, which is a theoretical additional risk factor for air leak. This study used more conservative flow levels, previously used safely in HiFlo therapy in patients with asthma [23]; therefore, the risk of air leaks was regarded as low. Air leaks in any of the following 3 manifestations were regarded as an SAE and prompted immediate reporting: pneumothorax, pneumomediastinum, or subcutaneous emphysema.Standard treatment–related AE: Vomiting, tachycardia, tremor, lactic acidosis, and others are known potential side effects of intravenous or inhaled bronchodilators that could be seen in both the HiFlo and standard care groups. Documentation of their occurrences was needed to evaluate the candidate secondary outcome measures (treatment-related side effects). If serious, they could be reported as SAEs.

Definitions of adverse events.Pneumothorax: single episode to be reported per patient.Pneumomediastinum: single episode to be reported per patient.Subcutaneous emphysema: single episode to be reported per patient.Vomiting: a period of sequential vomiting is considered a single episode, but if there is a pause of ≥4 hours, then the next occurrence is the start of a new episode.Tachycardia (heart rate ≥160 in children aged 2 to 4 years and ≥140 in those aged 5 to 11 years): an episode lasts for as long as the patient is in tachycardic range, but if there is a pause of ≥4 hours, then the next occurrence is the start of a new episode.Tremor: an episode lasts as long as any tremor is present, but if there is a pause of ≥4 hours, then the next occurrence is the start of a new episode.Lactic acidosis (venous or capillary lactate >2.2 mmol/L or arterial lactate >1.6 mmol/L): an episode starts every time an abnormal laboratory value is detected. The episode lactate value is recorded.Hypokalemia (potassium <3.5 mmol/L): an episode starts every time an abnormal laboratory value is detected.Sedation received to tolerate high-flow humidified oxygen (HiFlo) therapy: single episode to be reported per patient.Patient unable to tolerate HiFlo therapy (HiFlo discontinued): single episode to be reported per patient.Other: any other untoward medical occurrence or serious adverse event in a study participant.

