**Standard care group**
Commencing administration of the first, second, or third intravenous agentCommencing HiFlo therapyRe-escalating inhaled bronchodilator therapy to an hourly or more frequent dosageCommencing noninvasive ventilation with BiPAP ventilationIntubation for invasive ventilation

Candidate secondary outcome measures.Time (h) between presentation to the emergency department (ED) and the actual hospital dischargeTime (h) between presentation to the ED and achieving a Preschool Respiratory Assessment Measure (PRAM) [31] score of ≤3Time (h) between presentation to the ED and the ability to maintain oxygen saturation (SpO_2_) at ≥92% without supplemental oxygen or respiratory supportNeed for intravenous bronchodilator therapyDuration of intravenous bronchodilator therapyRequirement for noninvasive ventilationRequirement for invasive ventilation (intubation)Treatment-related adverse effects:Intravenous or inhaled bronchodilator–related side effects (eg, vomiting, tachycardia, and lactic acidosis)Poor compliance with HiFlo therapyHospital readmission within 48 hours of dischargeAcceptability and comfort scores for treatment during the episode (recorded using the end-of-study questionnaire and qualitative interview following the episode). These measures were codeveloped with the Lived Experience Advisory Panel before the trial commenced.

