#### Clinical Data Recording

The standard of care was guided by a well-defined wheezing or asthma care pathway for children agreed upon by the participating centers, which included various observations to aid with treatment decision-making. Key observations and assessments conducted and recorded for this study are summarized in Textbox 9 (a detailed description is available in section 6.7 of the study protocol in Multimedia Appendix 1).

Trial observations and assessments.Physical examination: this includes evaluation of suprasternal retraction, scalene muscle contraction, air entry, wheezing, work of breathing (respiratory distress), chest findings, and cardiovascular system findings.Vital signs: vital signs at initial assessment (triage) and during subsequent reassessments include respiratory rate, heart rate, oxygen saturation (SpO_2_), capillary refill time, and temperature.Preschool Respiratory Assessment Measure scoring: assessments required involve a physical examination and pulse oximetry, which are all routine procedures in the participating centers.Oxygen requirement: this includes monitoring of oxygen (O_2_) flow and fraction of inspired oxygen (FiO_2_).Blood gases: a proportion of patients may have blood gas measurements performed routinely. Specifically, partial pressure of carbon dioxide (pCO_2_) results (if available) will be used for treatment escalation decisions. In children, these will normally be measured using capillary or venous blood.

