### Statistics and Data Analysis

#### Statistical Analysis Plan

Participant flow through the trial will be represented in a CONSORT flowchart (Figure 1) according to the CONSORT extension for pilot and feasibility trials [41]. The available cases will be analyzed, following the intention-to-treat principles. Normally distributed variables will be summarized by means and SDs, skewed continuous variables by medians and IQRs, and categorical variables by frequencies and percentages. The difference in means between the trial arms for the primary and secondary outcomes will be estimated, together with bootstrapped 95% CIs. All analyses will be conducted using Stata (version 18; StataCorp LLC).

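### Each abnormal lactate or potassium result counts as a new adverse-event episode, so episode counts, and any between-arm difference in them, depend partly on how often blood was taken

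*Protocol article*

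**What the plan says.** Textbox 10 (Safety Reporting, Recording of AEs) uses three counting rules.

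- **Once per patient:** the three air-leak events, sedation to tolerate HiFlo, and HiFlo intolerance.
- **Merged over time:** vomiting, tachycardia and tremor. For tremor, "an episode lasts as long as any tremor is present, but if there is a pause of ≥4 hours" a new episode begins; the other two use the same 4-hour break.
- **Every result:** for lactic acidosis, "an episode starts every time an abnormal laboratory value is detected. The episode lactate value is recorded". The potassium entry reads "Hypokalemia (potassium <3.5 mmol/L): an episode starts every time an abnormal laboratory value is detected", with no mention of keeping the value.

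These records have a stated use. Recording of AEs says: "Documentation of their occurrences was needed to evaluate the candidate secondary outcome measures (treatment-related side effects". The candidate secondary outcomes (Textbox 5) list bronchodilator-related "side effects (eg, vomiting, tachycardia, and lactic acidosis" among their examples, without saying whether the unit is the child or the episode. The Statistical Analysis Plan section says: "The difference in means between the trial arms for the primary and secondary outcomes will be estimated, together with bootstrapped 95% CIs". It also allows frequencies and percentages for categorical variables.

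On sampling, Clinical Data Recording says only that "a proportion of patients may have blood gas measurements performed routinely". The schedule of events (Table 2) lists routine blood investigations during treatment, without an interval.

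**The concern.** Under the laboratory rule, one continuous disturbance sampled three times is three episodes. Under the rule for vomiting, tachycardia and tremor it would be one. With sampling left to routine care, the count reflects both how many abnormal results a child would produce and how many chances there were to find one.

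This matters between arms only if sampling differs between them. The article gives a reason to expect that it might. The trial is unblinded. Treatment Failure and Escalation describes an intravenous agent as the usual next step after failed burst therapy in standard care, while Study Design and Setting has HiFlo started in its place in the intervention arm. The Introduction names raised lactate and hypokalemia among the side effects of intravenous bronchodilators. If children on these agents are sampled more often, mean episodes would be inflated in standard care beyond any true difference in toxicity. The trial is also meant to define outcome measures for a definitive RCT, so a sampling-dependent definition could be carried forward.

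**Working it through.** The article gives no figure to reproduce. It gives no sampling frequency, abnormality rate or duration either, so all of these below are assumptions. From the article: 50 children allocated 1:1, hence about 25 per arm.

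**1. Same toxicity, different sampling.** Expected episodes per child = k × p, with k samples and probability p that a sample is abnormal.

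| p | k = 2 | k = 4 | ratio |
|---|---|---|---|
| 0.3 | 0.6 | 1.2 | 2 |
| 0.5 | 1.0 | 2.0 | 2 |
| 0.7 | 1.4 | 2.8 | 2 |

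The ratio of episodes is the ratio of samples, whatever p is.

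**2. Different toxicity, same sampling.** With k = 3 in both arms and p = 0.3 against 0.6: 3 × 0.3 = 0.9 against 3 × 0.6 = 1.8. The count does respond to toxicity.

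**3. One continuous disturbance per affected child.** Assume half the children in each arm have one abnormal period lasting 6 to 16 hours (mean 11), and all are sampled every h hours from a random start. Expected episodes = 0.5 × 11 / h.

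- h = 6: 0.5 × 11 / 6 = 0.92
- h = 3: 0.5 × 11 / 3 = 1.83

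Counting each disturbance once would give 0.5 in both arms. With 25 per arm, a normal-approximation 95% CI for the difference in mean episodes excludes zero in about 54% of trials, although there is no true difference. With the same interval and the same share sampled in both arms, the figure is about 5%.

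**4. The share of children tested also differs.** Take 50% tested 6-hourly against 90% tested 3-hourly, and assume that untested children contribute no episodes. The means become 0.5 × 0.92 = 0.46 and 0.9 × 1.83 = 1.65, and the CI excludes zero in about 80% of trials.

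**5. Does a per-child summary remove the problem?** In step 3, children with at least one abnormal value are 50% against 50%, because every abnormal period is at least as long as the sampling interval. In step 4, over all children, they are 0.5 × 0.5 = 25% against 0.9 × 0.5 = 45%; among those tested they are 50% against 50%, provided that testing is unrelated to risk. If successive results vary independently, detection still rises with sampling: 1 − (1 − p)^k at p = 0.3 gives 1 − 0.7² = 0.51 for two samples and 1 − 0.7⁴ = 0.76 for four. The per-child summary removes repeat counting but not every effect of sampling.

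**The case against.** The strongest reply is that Textbox 10 is a recording definition, not an analysis rule. The article does not fix episodes as the unit of comparison. The sentence on differences in means covers all outcomes, several of them plainly binary, and percentages of affected children are equally open. The choice may be settled in a statistical analysis plan, or in the safety section of the full protocol, neither of which is shown. Recording every abnormal result is also the finer capture and can be collapsed to one indicator per child. All of this stands, and it limits the point to any analysis based on episodes. It does not alter the stated counting rule, which makes laboratory episodes sampling-dependent and unlike the clinical episodes listed beside them.

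Three stronger readings are tempting but not supported.

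- **That the comparison measures sampling instead of toxicity.** Step 2 shows that the count responds to both.
- **That untested children are scored as zero.** The article does not say so. It says available cases are analyzed, which leaves room to treat them as missing for laboratory outcomes.
- **That the arms were in fact sampled differently.** This is an inference. Intravenous agents were allowed in both arms, could precede randomization, and might not be given directly in standard care. If intravenous use did differ, true toxicity might differ too.

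The ratios in the working are the sampling ratios that were put in. They show what the rule can do, not what happened in this trial.

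**Conclusion.** The point holds in limited form. Lactate and potassium episodes are counted per abnormal result, with no merging rule and no stated sampling interval, so episode counts and any difference in mean episodes depend partly on how often blood was taken. If sampling differs by arm, the comparison is biased by an amount the article does not allow one to estimate. With identical toxicity and a twofold difference in sampling, mean episodes would differ twofold.

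The consequence is modest. This is one component of a candidate secondary outcome in a feasibility trial of 50 children, it is reported as an estimate with a CI, and none of the four progression conditions uses it. It is still worth correcting, because the main correction needs only records already held.

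**What to change.** For lactic acidosis and hypokalemia, compare the number of children with at least one abnormal value instead of the number of episodes, and add the worst recorded lactate per child. Show the number of children tested by arm, and the number of samples where available. Interpret the proportion among tested children cautiously: being tested may itself relate to risk, and more samples raise the chance of detection.

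Cost: recruitment is complete and the article describes the data as under analysis, so this is a change of derivation and reporting. The per-child indicator follows from the episode records, and the worst lactate from the recorded values. Numbers tested and sampled may need local laboratory data, because the article does not say that normal results were captured. The raw episode count is lost as a comparative measure.

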#### Responsibilities of Safety Reporting

The PI at each site was responsible for reporting any SAE or SAR to the clinical trials unit (CTU). The trial manager (TM) was responsible for ensuring that all SAE and SAR reports were complete and accurate and for following up with the research teams to ensure this. The TM was responsible for maintaining and updating all the SAE and SAR records required for reporting to the sponsor and the Research Ethics Committee (REC). All AEs and SAEs were monitored by the TM at the CTU and reported and reviewed at the trial steering committee (TSC) meetings.

### Statistics and Data Analysis

#### Statistical Analysis Plan

Participant flow through the trial will be represented in a CONSORT flowchart (Figure 1) according to the CONSORT extension for pilot and feasibility trials [41]. The available cases will be analyzed, following the intention-to-treat principles. Normally distributed variables will be summarized by means and SDs, skewed continuous variables by medians and IQRs, and categorical variables by frequencies and percentages. The difference in means between the trial arms for the primary and secondary outcomes will be estimated, together with bootstrapped 95% CIs. All analyses will be conducted using Stata (version 18; StataCorp LLC).

#### Qualitative Data Analysis

The interview transcripts will be anonymized and transcribed verbatim. Thematic content analysis will be performed on the interview transcripts based on a 14-stage structured approach [42]. The initial codes will be semantically clustered into subthemes, and finally, these subthemes will be clustered into main themes. The final thematic structure will be described and supported with illustrative interview quotes.

#### Subgroup Analyses and Participant Population

Subgroup analysis will be limited to 3 variables on which randomization was stratified: site, age, and severity of acute episode. The analysis will be conducted on an intention-to-treat basis; all the recruited participants with consent received will be included in the analysis. In addition, we will examine the screening logs at the sites to identify factors involved in the failure to recruit, which may be relevant to the design of the full RCT. Furthermore, per-protocol analysis will be performed, in which deviation from the trial protocol will result in exclusion from data analysis from that point of protocol deviation onward. Examples of protocol deviations include the following:

A child is randomized to the HiFlo therapy arm, but for logistical reasons (eg, no equipment is available), this therapy never commenced.A child in the HiFlo arm is commenced on therapy, which is later discontinued or changed to another modality because of transfer to a ward area that is unable to provide this care.

The per-protocol analysis will be interpreted cautiously because of the small sample size.

### Data Management

A research team pack was used to ensure accurate data collection and included clinical observation sheets and case report forms to record the outcome data. Pseudonymized data were electronically entered by trained research nurses at each site onto a web-based, password-protected data management system (REDCap; Research Electronic Data Capture; Vanderbilt University) designed by a data manager from the Brighton and Sussex CTU (BSCTU). The data manager oversaw data quality and ensured that the database was ready for analysis. Once the data had been cleaned and the database locked, they were transferred securely to the trial statistician for descriptive analysis by the trial arm.

It was agreed that all investigators and trial site staff must comply with the requirements of the General Data Protection Regulation 2018 guidance for researchers—Health Research Authority (HRA) [54]. A specific data management plan and a monitoring plan were developed for this study (available from BSCTU). Archiving will be authorized by the sponsor following the submission of the end-of-trial report. All essential documents will be archived for a minimum of 5 years after trial completion. Destruction of essential documents will require authorization from the sponsor.

### Trial Management and Monitoring

The BSCTU oversaw the management of the study. A TM worked closely with the chief investigator (CI) and research team to ensure that the timelines were met, recruitment was tracked, and remote monitoring was undertaken for quality assurance. The TM supported the setup of the sites, ensuring that all documentation and processes were in line with the research governance and HRA processes. Monthly trial management group (TMG) meetings with the CI, DM, statistician, PIs, and research nurses from the sites were conducted to oversee the study’s progress.

The TSC consisted of the TMG and 3 independent members (a lay member—parent of a child with asthma, a pediatrician with relevant expertise, and a statistician). The TSC reviewed the reports from the TMG and met to oversee the overall progress. With its independent membership, the TSC also reviewed the data and safety issues, fulfilling the role of this feasibility trial of a data and safety monitoring board. Financial management for the study was overseen by the TM with institutional supervision by the head of research at the UHSx NHS Foundation Trust.

### Ethical Considerations

The study protocol and all applicable documents and amendments were approved by the West Midlands–Solihull Research Ethics Committee (REC) and the Health Research Authority (HRA) according to applicable regulations (REC reference: 19/WM/0219, IRAS: 261627). This study was registered with International Standard Randomised Controlled Trial Number registry (ISRCTN78297040) [55]. The HiFlo ASA project proposal was successful in competition 35 of the NIHR Research for Patient Benefit Program after 2 stages of independent peer review by the program’s designated expert advisory panel. The study protocol for this feasibility study was further developed and discussed by researchers from the participating centers, with the involvement of the BSCTU.

### Dissemination

In this feasibility trial, the important aspects of dissemination concern the use of trial data in designing a full RCT and preparing an application to fund it. Therefore, dissemination will be principally among the study team, the PPI groups involved, and the stakeholders (both professional and patient or parent groups) to be involved in the full multicenter RCT. We intend to publish a protocol for this feasibility trial.

### Trial Sponsorship

The sponsor was responsible for ensuring that the trial was being conducted under appropriate governance. The sponsor is the UHSx NHS Foundation Trust.

### Committees

The composition, roles, and responsibilities of the TMG, TSC, and LEAP are described in the *General Information* section (part 6) at the beginning of the study protocol in Multimedia Appendix 1.

### PPI Group

PPI was sought at different stages in the development of the study, with a plan for continuing input during the research and its dissemination.

The detailed involvement of the following PPI groups is described in section 11.3 of the study protocol in Multimedia Appendix 1:

Two local patient groups from Kent, Surrey, and Sussex (KSS), funded by the NIHR, participated in the trial design and will be informed of the findings of the study: KSS young people’s advisory group and KSS parent and carer advisory group (KSS, Generation R).A separate NIHR research support grant enabled the creation of a LEAP—a group of 6 to 8 parents whose young children have been admitted with ASA, together with 4 children with experience of ASA—to provide disease-specific PPI into the study.

## Results

The trial was opened to recruitment at the lead site in February 2020, but a month later, the COVID-19 pandemic reached the United Kingdom, and the study was put on hold in March 2020. There was a 15-month pause because of a combination of factors, including general concerns about face-to-face research, specific concerns about HiFlo therapy as an *aerosol-generating procedure*, and redeployment of research staff to clinical duties during the pandemic. The trial was reopened at the lead site in July 2021 and opened at the other 3 sites between August and December 2022. The follow-up was completed in July 2023. The results are currently being analyzed and will be reported separately.

## Discussion

This paper describes the protocol for a multicenter feasibility RCT of 50 children that has been successfully executed at 4 sites in the United Kingdom. The trial aimed to establish whether a full RCT of early HiFlo therapy in ASA can be conducted successfully and safely and whether recruitment for such a trial, using deferred consent, is practicable in children aged 2 to 11 years presenting to hospital with ASA. If it is determined that a definitive RCT is feasible, the data from the study will inform the outcome measures and sample size needed for adequate power.

A total of 2 previous pilot RCTs of HiFlo therapy in acute asthma have been published [27,28], but neither provided the feasibility data required to design a definitive RCT to assess the clinical effectiveness. Both studies used an asthma severity score as the main outcome measure, but neither the *Pulmonary Score* used by Ballestero et al [27] nor the *Pulmonary Index Score* used by Gauto Benítez et al [28] were referenced, and it is unclear what any differences in these outcomes would mean for clinical management. In this protocol, we chose 2 candidate primary outcome measures that had been determined by clinicians and by parents and children to be meaningful and likely to impact practice. Both the need for escalation of therapy owing to treatment failure and the time to reach readiness for discharge are important in determining resource use and care costs.

We used an asthma scoring system and selected PRAM because it was the only asthma scoring system validated across the entire age range of 2 to 11 years. At least 17 different asthma severity scores have been published, but few EDs in the United Kingdom regularly use any of them as part of routine clinical practice [56], and only one of our sites had any prior familiarity with PRAM. The study protocol used the PRAM score in 2 ways: as one of the entry criteria (PRAM score ≥5 after first-line treatment) and as a candidate (secondary) outcome measure (time to achieve a PRAM score of ≤3). As noted above, implementing PRAM at the study sites and maintaining PRAM competency, despite high staff turnover, required considerable input of training resources. The advantage of using a validated asthma score as an entry criterion was that it standardized the severity of acute asthma in children entering the study, allowed comparison with other acute asthma trials [36], and allowed us to stratify randomization by asthma severity at entry. A potential disadvantage was that it risked reducing out-of-hours recruitment owing to PRAM-trained staff not being available.

As with many clinical trials since 2019, the conduct of this study was severely affected by the COVID-19 pandemic. It was necessary to pause recruitment for a prolonged period because of general logistic issues affecting all clinical research and specific concerns relating to the theoretical risks of aerosol generation and COVID-19 transmission from HiFlo therapy. The experience gained by the research team (both in adapting trial procedures and disseminating new research findings on aerosol generation) to allow the successful completion of the trial will be valuable in planning a definitive RCT.

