To assess the acceptability of HiFlo^b^ therapy and the deferred consent model to children, parents, and staff	Satisfaction ratings on the end-of-study questionnaire	Discharge

^a^ASA: acute severe asthma.

^b^HiFlo: high-flow humidified oxygen.

Candidate primary outcome measures.Treatment failure needing escalation of therapy as defined in the *Treatment Failure and Escalation* section.The time (h) between presentation to the emergency department and meeting hospital discharge criteria as defined by the following criteria:The ability of the child to maintain arterial oxygen saturation (SpO_2_) measured by pulse oximeter at ≥92% without supplemental oxygen or respiratory support for a 4-hour periodThe ability of the child to remain clinically stable for a minimum of 4 hours between inhaled bronchodilator dosesThe ability to maintain these conditions continuously until hospital discharge

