### Hospital Discharge

#### Hospital Discharge Criteria

It was recognized that the timing of discharge from hospital is affected by multiple factors in addition to the child’s medical condition; therefore, criteria of fitness for discharge were defined as a more robust and reproducible candidate primary outcome measure in addition to actual hospital discharge, which was used as a candidate secondary outcome measure. Hospital discharge criteria are defined in Textbox 7.

Hospital discharge criteria.The ability of the child to maintain arterial oxygen saturation (SpO_2_) measured by pulse oximeter at ≥92% without supplemental oxygen or respiratory support for a 4-hour periodThe ability of the child to remain clinically stable for a minimum of 4 hours between inhaled bronchodilator dosesMaintaining these conditions continuously until hospital discharge

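### Candidate primary outcome 2 still depends in part on discharge logistics, because its third criterion runs until the child actually leaves hospital

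*Protocol article*

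**What the plan says.** Candidate primary outcome 2 (Textbox 1, under Primary Feasibility Objectives and Outcome Measures) is "The time (h) between presentation to the emergency department and meeting hospital discharge criteria". Three criteria follow:

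1. saturation of at least 92% without oxygen or respiratory support over 4 hours;
2. clinical stability for at least 4 hours between inhaled bronchodilator doses;
3. both conditions kept up without interruption until the child is discharged.

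Textbox 7, under Hospital Discharge Criteria, repeats all three.

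That section also gives the reason for the outcome. It notes that "the timing of discharge from hospital is affected by multiple factors in addition to the child’s medical condition" and says that for this reason "criteria of fitness for discharge were defined as a more robust and reproducible candidate primary outcome measure". Actual discharge is kept as a candidate secondary outcome (Textbox 5). The Discussion describes the outcome as readiness: "the time to reach readiness for discharge are important in determining resource use and care costs".

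**The concern.** The first two criteria have a 4-hour window that depends on the child's condition. The third has a window that closes at actual discharge, the event that the article describes as subject to non-medical influences. Whether an earlier qualifying time stands can be settled only when the child leaves.

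Take two children who first satisfy criteria 1 and 2 at the same hour. One goes home promptly and keeps that time. The other waits overnight for a reason unrelated to illness, and so is exposed for longer to a low saturation reading or an early bronchodilator dose. If one occurs, the natural reading of criterion 3 is that the earlier time is lost and the child must qualify again.

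The trial exists to choose outcome measures and to estimate their variability for a definitive RCT (Objective; Table 1; Sample Size and Planned Recruitment Rate). If part of the spread in this outcome reflects how long children wait to leave, the SD carried forward includes that part. Four sites and unblinded care (Study Design and Setting) leave room for the wait to differ by site or by arm.

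**Working it through.** The article gives no numerical claim to reproduce here. The first step is to compare the texts; the second is an illustration of size.

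**Texts side by side**

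- Purpose (Hospital Discharge Criteria): discharge timing has non-medical causes, so a fitness measure is used, described as more robust and reproducible.
- Definition (Textboxes 1 and 7): criteria 1 and 2 have 4-hour windows; criterion 3 is open-ended and closes at discharge.
- Nothing in the article closes the third window earlier or says how a lapse during a non-medical wait is handled.

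The direction follows: with any non-zero lapse rate, a longer wait raises the chance that the first qualifying time is lost. With no wait, the effect is nil.

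**Inputs for the illustration**

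- Observations every 4 h. PRAM is scored 4-hourly on the ward (PRAM Scoring and Training), and scoring involves pulse oximetry (Textbox 9).
- Assumed: probability p of a lapse at each observation, 3% to 10%.
- Assumed: wait W between first meeting criteria 1 and 2 and leaving, 2, 12 or 16 h.
- Assumed: recorded time moves to the last lapse plus 4 h. Observations start at a random point in the 4-hour cycle.

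**Wait of 12 h** (three observations, at mean times 2, 6 and 10 h)

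- P(reset) = 1 − (1 − p)³. For p = 0.03 this is 8.7%; for p = 0.10 it is 27.1%.
- Mean shift = 14p + 10p(1 − p) + 6p(1 − p)².
  - p = 0.03: 0.420 + 0.291 + 0.169 = 0.88 h.
  - p = 0.10: 1.400 + 0.900 + 0.486 = 2.79 h.
- This lets some children requalify after the wait has ended. Their share of those reset is p / P(reset): 0.03/0.0873 = 34% to 0.10/0.271 = 37%. Capping the recorded time at 12 h changes the 14 to 12 and gives 0.36 + 0.291 + 0.169 = 0.82 h and 1.20 + 0.90 + 0.486 = 2.59 h.
- Taking both treatments together: about 0.8 to 2.8 h.

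**Wait of 2 h** (an observation falls in the wait with probability 2/4, at mean time 1 h)

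- P(reset) = 0.5p = 1.5% to 5%.
- Mean shift = 0.5p × 5 = 0.075 to 0.25 h. Every reset child here requalifies after the wait; capping at 2 h gives 0.5p × 2 = 0.03 to 0.10 h.

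**Wait of 16 h** (four observations)

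- P(reset) = 1 − (1 − p)⁴ = 11.5% to 34.4%.
- Mean shift = 18p + 14p(1 − p) + 10p(1 − p)² + 6p(1 − p)³ = 1.39 to 4.31 h; capped (16 in place of 18), 1.33 to 4.11 h.

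**Compared with actual discharge.** A 12 h wait moves actual discharge by 12 h. It moves outcome 2 by 0.82/12 = 7% to 2.79/12 = 23% of that. At 16 h the share is 1.33/16 = 8% to 4.31/16 = 27%.

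**Cross-check with a constant hourly lapse rate r.** P(reset) = 1 − exp(−rW). At W = 12 h, r = 0.5%, 1%, 2% and 5% per hour give 5.8%, 11.3%, 21.3% and 45.1%, with simulated mean shifts of 0.58, 1.14, 2.20 and 4.78 h. The direction is the same; the size follows the assumed rate.

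**The case against.** Several points on the other side are sound.

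- **The article's claim is relative.** It says more robust than actual discharge, not immune to logistics. A reader might infer that the claimed robustness fails. The documents do not support that: a child with no lapse keeps the earlier time, and on the assumed rates the outcome removes roughly three quarters or more of the dependence on the wait.
- **Sustained recovery is a legitimate endpoint.** A child who lapses after a first stable 4 hours may not have been ready. A reader might infer that criterion 3 is a mistake to be replaced. It is a trade-off: first attainment frees the outcome from the wait but credits transient recoveries. The weakness is only that the window's length is set by discharge.
- **The reset is inferred.** The article does not say that one low reading or one early dose restarts the time, and criterion 2 speaks of the child's ability to remain stable. The full protocol (Multimedia Appendix 1) is not shown and may contain an operational rule.
- **It is partly covered.** Textbox 5 lists time to maintaining saturation without oxygen or support, with no until-discharge clause. That helps with criterion 1 but leaves bronchodilator spacing aside.
- **Bias between arms is not shown.** Nothing in the article says that children are observed for longer after HiFlo stops, or that sites discharge differently. It remains a possibility.

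What survives is narrower: the third window is closed by the event whose timing the outcome was meant to be protected from, and the article does not resolve this.

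**Conclusion.** The point holds as a limited weakness in an outcome definition. Outcome 2 retains some dependence on how long a child waits to leave, in a known direction and of unknown size. The range of about 0.8 to 2.8 h for a 12 h wait, and 0.25 h or less for a 2 h wait, rests entirely on the assumed lapse probabilities and waits, on the 4-hourly grid, and on reading criterion 3 as a reset rule. With short waits the effect is negligible.

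It would be tempting to turn this into a sample-size penalty for the definitive RCT. That would need an outcome SD, which the article does not give, and a wait that is the same for every child and unrelated to the underlying recovery time. No such figure is claimed here. The matter deserves attention because this trial was set up to compare candidate outcomes and estimate their variability, and its data can answer the question directly.

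**What to change.** For analysis only, with no change to bedside discharge decisions:

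1. Keep the current definition of candidate primary outcome 2.
2. From the same recorded observations, also derive the time at which criteria 1 and 2 were first held together for the 4-hour period already stated, whatever the discharge time.
3. Report, by arm and site, the proportion of children with a later lapse before discharge.
4. Compare the variability of the two versions, and how each relates to the wait before discharge, when choosing the outcome and SD for the definitive RCT.

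The Results section says that analysis was still under way, and no new assessments are needed, so the cost is a little extra derivation work. The drawback is that the first-attainment version counts some transient recoveries; the lapse proportion makes these visible. If the full protocol already states how a lapse before discharge is handled, that rule should be cited beside the definition.
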